## Abstract

**Background:**

Removal of uraemic toxins is inadequate using current dialysis strategies. A new class of dialysis membranes have been developed that allow clearance of larger middle molecules. The REMOVAL-HD study (a tRial Evaluating Mid cut-Off Value membrane clearance of Albumin and Light chains in HaemoDialysis patients) will address safety, efficacy and the impact on patient-centred outcomes with the use of a mid cut-off (MCO) dialyser in a chronic haemodialysis (HD) population.

**Methods:**

REMOVAL-HD is an open label, prospective, non-randomised, single-arm, multi-centre device study in 85 chronic HD participants. All visits will be conducted during regular HD sessions and participants will undergo a 1 month wash-in period using a standardised high flux dialyser, 6 months of intervention with a MCO dialyser and 1 month of wash-out using a high flux dialyser. The primary endpoint is change in pre-dialysis concentrations of serum albumin, with secondary endpoints including the efficacy of clearance of free light chains and β-2 microglobulin, and patient-centred outcomes including quality of life, symptom burden, functional status, nutritional status, hospitalisation and death.

**Discussion:**

MCO dialysers are a novel form of HD membrane. The REMOVAL-HD study is a pivotal study designed to monitor the immediate and medium-term effects following exposure to this dialyser.

**Trial registration:**

Australian New Zealand Clinical Trials Registry Number (ANZCTRN) 12616000804482. Date of registration - 21/06/2016.

## Background

Haemodialysis (HD) remains a principal renal replacement modality for patients with end stage kidney disease (ESKD). Despite the efficacy of HD as a treatment to replace essential kidney functions, such as fluid and acid-base balance, the morbidity and mortality of patients receiving HD remain high when compared with those of the general population [1, 2]. The inadequate removal of uraemic toxins, particularly those in the middle molecule range (0.5–60 kDa), may play a role in this phenomenon [3]. Middle molecules are an important class of uraemic solutes which have been linked to reduced survival associated with ESKD [3, 4].

With the advent of high-flux dialysers and haemodiafiltration (HDF), the number of middle-molecules removed by chronic HD programs has continually increased but current HD processes principally only remove molecules with molecular weight cut-offs between 10 to 20 kDa [5]. There are still over 20 middle-molecules that are inadequately removed by current dialysis strategies but are potential contributors to chronic inflammation, cardiovascular disease, secondary immunodeficiency and reduced quality of life in dialysis patients [6, 7].

In recent years, there has been increasing interest in the development of new generations of dialysis membranes that will allow more effective removal of larger middle molecules. High cut-off HD membranes, with pore sizes of 8 to 10 nm, have been shown to improve clearance of larger solutes [8]. However, the use of high cut-off membranes was associated with substantial albumin loss and supplementation with human albumin solution was recommended at the end of each dialysis session [6]. These membranes were therefore deemed unsuitable in the setting of chronic HD.

A mid cut-off (MCO) dialyser (such as Theranova) has a pore size and molecular weight cut-off intermediate between those of either a high flux or a high cut-off membrane. MCO membranes are designed to provide increased clearance of larger middle-molecules in chronic HD patients, compared with high flux HD. Short term clinical studies following 4 dialysis sessions have demonstrated effective removal of molecules up to the molecular weight (MW) of 45 kDa [9]. However, these studies also identified a greater loss of albumin (MW 66.5 kDa) compared to high-flux dialysis and HDF [9]. It is currently unknown if this degree of albumin loss is transient or will be tolerated in chronic dialysis patients. Sustained albumin loss is a concern for a chronic dialysis treatment as hypoalbuminemia is strongly associated with increased morbidity and mortality in patients receiving HD [10]. In addition, to date clinical outcomes have not yet been studied with the sustained use of a MCO dialyser.

Thus, the purpose of the REMOVAL-HD study is to determine safety and efficacy of the MCO dialyser (Theranova; Baxter Healthcare, Sydney, Australia) in a chronic HD population over 6 months. This study will assess the efficacy of MCO dialysis regarding the clearance of larger middle-molecules, and determine its safety with regards to its effect on serum albumin.

## Methods/design

### Study aims

The primary objective of the REMOVAL-HD study is to determine the change in pre-dialysis concentrations of serum albumin in participants undergoing chronic HD using the MCO Theranova dialyser between baseline and 6 months. This study will also examine the trend of serum albumin change over the 6-month treatment period and the proportion of participants with a drop in serum albumin of > 5% below their baseline value. The study will also assess the efficacy of clearance of the three middle molecules: lambda free light chains (lambda-FLC, MW 45 kDa), kappa free light chains (kappa-FLC, MW 22.5 kDa) and β-2 microglobulin (MW 11 kDa).

### Study design and setting

REMOVAL-HD is an investigator led, open label, non-randomised, single-arm, multi-centre device study. The study will involve 85 participants from 9 in-centre haemodialysis units in Australia and New Zealand. Table 1 summarizes the inclusion and exclusion criteria for the REMOVAL-HD study. Participants with urine output< 500 mL were included to minimise differences in clearance of measured molecules by residual renal function. The study is coordinated and supported by the Australasian Kidney Trials Network (AKTN) Fig. 1. demonstrates the overall study timeline. The study commenced in January 2017 and successfully completed recruitment in August 2017.

**Table 1 Tab1:** Inclusion and exclusion criteria for the REMOVAL-HD study

Inclusion criteria
1. Established chronic in-centre haemodialysis (HD) patient (> 12 weeks on HD)
2. Aged over 18 years
3. Has a functioning Arteriovenous Fistula or Graft
4. Either oliguric (< 500 mL/24 h based on 24 h urine collection within 12 weeks of screening) or anuric
5. Able to give informed consent
Exclusion criteria
1. Planned renal transplant within study intervention period
2. Planned conversion to peritoneal dialysis or transfer to another dialysis unit within study intervention period
3. Active chronic infection or significant active inflammatory conditions including autoimmune disease, inflammatory arthritis and active malignancy
4. Life expectancy < 12 months
5. Pregnancy or breast feeding
6. Indication for haemodiafiltration (HDF) according to treating physician
7. Dialysis catheter in situ
8. Receiving immunosuppressant medication
9. Current use of nutritional or dietary supplements to increase or reduce protein intake including protein powder or weight loss supplements and is unable to cease the supplement
10. Serum albumin < 30 g/L (within 4 weeks of screening)
11. Inability to complete study assessments

**Fig. 1 Fig1:**
[figure not shown]
Overall study timeline

### Ethical considerations

Ethical approval has been obtained from Institutional Ethics Committees (IEC) for each participating site (Protocol version 1.3 11th November 2016). The study will be performed in accordance with the 2013 Fortaleza, Brazil 7th Revision of the Declaration of Helsinki, the National Health and Medical Research Council (NHMRC) Statement on Ethical Conduct of Human Research (2015), Joint NHMRC/AVCC Statement and Guidelines on Research Practice (1997), applicable ICH guidelines, ISO 14155:2011 and Note for Guidance on Good Clinical Practice (CPMP/ICH/135/95) annotated with Therapeutic Goods Administration (TGA) comments. Informed signed consent will be obtained from all participants. This study is registered with Australian and New Zealand Clinical Trials Registry (ANZCTRN 12616000804482).

### Study procedures

The timing of the study visits and changes in study treatment are shown in Fig. 2. All visits will occur when participants attend their usual HD session. Participants will undergo a wash-in, intervention and wash-out period, as outlined below.

**Fig. 2 Fig2:**
[figure not shown]
Timing of visits and changes in study treatment

#### Wash-in period (week 0–4)

Enrolled participants will receive a 4-week wash-in period using a high-flux dialyser (Revaclear; Baxter Healthcare, Sydney, Australia).

#### Intervention period (week 4–28)

Participants will then receive 24 weeks of treatment with a MCO dialyser (Theranova; Baxter Healthcare, Sydney, Australia) three times per week.

Although dialysis prescriptions will remain under the supervision of the local nephrology team, the following treatment guidance is provided:target blood flow > 300 mL/min;dialysate flow rate 500 mL/min;dialysis session length and frequency to remain unchanged; andfluid removal according to participant’s individual prescription.

#### Wash-out period (week 28–32)

Participants will then receive a 4-week wash-out period using the Revaclear high flux dialyser.

### Data collection and outcome measures

The study visit schedule and timing of data collection are summarized in Table 2. Demographic and medical history, including age, gender, height and weight, race, blood pressure, heart rate, cause of ESKD, comorbidities, dialysis and medication history will be collected. Blood samples will be taken pre-dialysis at the mid-week HD session for local and central laboratory testing. Central samples will be centrifuged and stored at − 80 °C until analysed.

**Table 2 Tab2:** Visit schedule for REMOVAL-HD study

Study Phase	Screening	Wash in Period		Intervention							Wash out
Visits	Visit 1	Visit 2	Visit 3 Baseline	Visit 4	Visit 5	Visit 6	Visit 7	Visit 8	Visit 9	Visit 10	Visit 11
	Week −1	Wk 0	Wk 4	Wk 6	Wk 8	Wk 12	Wk 16	Wk 20	Wk 24	Wk 28	Wk 32
Screening											
Inclusion/exclusion criteria	X	X									
Informed Consent	X										
24 h Urine collection	X										
Demographics/Medical History/Physical exam		X									
Primary Outcome											
Centrally tested serum albumin^a^		X	X	X	X	X	X	X	X	X	X
Trial Intervention Use											
High Flux (Revaclear) dialyser		X	X							X	X
Mid cut-off (Theranova) dialyser			X	X	X	X	X	X	X	X	
Clinical assessments											
Erythropoietin Resistance Index			X				X			X	
Weight (pre & post HD)			X				X			X	X
Duration of HD			X				X			X	X
Restless Leg Symptom Rating Scale			X				X			X	
Malnutrition Inflammation Score			X				X			X	
Edmonton Symptom Assessment System Revised			X				X			X	
6 min walk test^a^			X				X			X	
Adverse events (as required)		X	X	X	X	X	X	X	X	X	X
Local lab assessments											
Albumin^a^		X	X	X	X	X	X	X	X	X	X
Urea (pre & post HD)			X				X			X	
Haemoglobin, transferrin, INR, APTT^a^			X				X			X	
Central lab samples											
Lambda free light chains^a^		X	X	X	X	X	X	X	X	X	X
Κappa-FLC, β2Microglobulin, high sensitivity C-Reactive Protein^a^			X				X			X	
Substudy – Matrix Gla Protein, fetuin A, CPP, FGF23^a^			X				X			X	

^a^ Collected pre-dialysis prior to the mid-week HD

*APTT* activated partial thromboplastin time, *CPP* calciprotein particles, *FGF23* Fibroblast growth factor23, *HD* haemodialysis, *INR* international normalised ratio

#### Primary outcome measure

The primary outcome is change in pre-dialysis serum albumin between baseline and at 6 months. The study will also monitor the trend of changes in pre-dialysis concentrations of serum albumin during the intervention period. Serum albumin levels for these analyses will be obtained from central laboratory testing following completion of all study visits. Serum albumin will also be monitored at every visit locally to record safety data, including any large reduction (> 25%) in serum albumin level.

#### Secondary outcome measures

Change in centrally tested middle molecules, including lambda-FLC, kappa-FLC and β-2 microglobulin.Change in inflammatory marker (high sensitivity C-Reactive Protein) and coagulation profile [international normalised ratio (INR) / (activated partial thromboplastin time (APTT)].Erythropoietin resistance index (ERI) in participants taking erythropoietin (EPO) (ERI ≥1.0 IU/kg/week/gHb) or darbepoetin (DPO) (ERI ≥0.005 μg/kg/week/gHb).Assessment of dialysis related symptoms:Restless leg syndrome [Restless Legs Syndrome Rating Scale (RLSRS)].Quality of life [Edmonton Symptom Assessment System Revised (ESAS-R)] [11].Functional status with 6-min walk test – the distance a participant can achieve by walking on a flat surface in 6 min is measured using trundle wheel.Nutritional status using Malnutrition Inflammation Score (MIS) [12].Number and duration of all-cause hospitalisations.Number of infection-related hospitalisations.All-cause mortality.

#### Exploratory outcome measures

The impact on circulating levels of calcification regulatory proteins, including matrix Gla protein (MGP), fetuin-A, calciprotein particles (CPPs) and fibroblast growth factor 23 (FGF23) will be explored.

#### Frequency of measurement of biomarkers

Serum albumin and lambda FLC measurement will be evaluated at every study visit. However, the remaining assessments will be performed at baseline, midway through the study and at completion of the intervention period (Table 2).

### Sample size estimation

The study has been powered to identify a change of 5% in serum albumin concentrations from a median baseline level of 35 g/L (standard deviation of 5 g/L). A 5% decline in serum albumin has been shown to be associated with a doubling of mortality risk in haemodialysis patients [13]. To detect this change with 80% power at the 5% significance level, a sample size of 72 is needed. Allowing for a 15% loss to follow-up, a minimum of 85 participants need to be recruited to achieve the required sample size.

### Statistical analysis approach

The 95% confidence interval for the mean difference in central serum albumin between 6 months and baseline will be used to assess the change in albumin: a clinically non-meaningful reduction in albumin due to MCO dialysis will be inferred if the lower limit of the confidence interval excludes a reduction in serum albumin that is equal to or exceeds 5% of the median serum albumin at baseline. Change in serum albumin levels over the entire intervention period (weeks 4 to 28) will be analysed using a linear mixed-effects regression model. This analysis will be adjusted for baseline serum albumin levels. Other continuous secondary outcome variables will be analysed using the same methods described above. Secondary outcomes that are categorical will be analysed using McNemar’s test for comparisons between 6 months and baseline and generalised estimating equations for trends across the intervention period. Serious adverse events (SAE), serious adverse device effects (SADE) and unanticipated serious adverse device effects (USADE) will be presented as number (percent) to assess the safety of the MCO dialyser. All hypothesis tests will be assessed at 5% level of significance.

### Safety reporting

For the purposes of this study, the period of observation for collection of treatment-related SAEs will be from the start of the wash-in period until the end of the wash-out period. All SAEs will be recorded regardless of whether they are related to the study intervention. SADEs, USADEs and SAEs will be recorded as part of the regular data collection activities of the trial.

### Data monitoring

Safety will be examined through close monitoring of data from individual participants rather than through statistical comparison. This will be achieved by continuous monitoring of serum albumin for any large reductions from baseline (> 25%) in serum albumin level. It will be the responsibility of the Trial Steering Committee (TSC) to protect the safety of trial participants and the scientific integrity of the trial by overseeing the monitoring of albumin levels, SAEs and operational data. For the purpose of data validation, the principal investigators will permit a member of the AKTN or its designee to inspect the source data and compare them with the case report forms. Notification of these audits will be sent to all investigators in advance.

### Discontinuation of study invention

Participants will revert to high-flux HD/HDF at any stage if any of the following occur:an unexplained reduction in pre-dialysis serum albumin of > 25% at 2 consecutive treatment visits compared to baseline level. Potential explanations for reductions in albumin levels may include infections and inflammatory conditions, such as autoimmune disease, inflammatory arthritis and malignancy;failure to maintain adequate HD dose measured according to local guidelines;at the discretion of the treating physician.

When withdrawn from the study intervention, participants will continue to be followed up as per the trial procedures.

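### The albumin conclusion is attributed to MCO dialysis, but nothing in the decision rule separates week-28 values from participants already returned to high-flux HD or HDF

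*Protocol article*

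**What the plan says.** Under Statistical analysis approach, the protocol article rests its conclusion on "The 95% confidence interval for the mean difference in central serum albumin between 6 months and baseline". If the lower limit "excludes a reduction in serum albumin that is equal to or exceeds 5% of the median serum albumin at baseline", then "a clinically non-meaningful reduction in albumin due to MCO dialysis will be inferred". Study aims likewise frames the primary objective as albumin change in people dialysed with the MCO device.

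Under Discontinuation of study invention: "Participants will revert to high-flux HD/HDF at any stage if any of the following occur". The listed reasons are an unexplained albumin fall of more than 25% from baseline at two consecutive treatment visits, failure to maintain dialysis dose, and the treating physician's discretion. The section ends: "When withdrawn from the study intervention, participants will continue to be followed up as per the trial procedures". Table 2 schedules central albumin at every visit from week 0 to week 32, so a participant off MCO still has a week-28 sample due.

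The Background says that short-term studies found greater albumin loss on MCO than on high-flux dialysis or HDF. Statistical analysis approach also plans a linear mixed-effects model of albumin over weeks 4 to 28.

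**The concern.** The decision rule and the follow-up rule answer different questions. The rule draws a conclusion about MCO dialysis. Continued follow-up yields a week-28 value for everyone who started MCO, whatever they are receiving by then.

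One trigger for leaving MCO is the primary outcome itself. That trigger applies only to falls with no other explanation, which are the falls most plausibly related to the device. Reversion at physician discretion may also follow a falling albumin, because the trial is open label and local albumin is checked at every visit.

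A participant who leaves MCO for these reasons and recovers on a treatment with less albumin loss contributes a small week-28 change, although the change on MCO was large. In a rule of the non-inferiority type, this pulls the interval toward a finding of safety.

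**Working it through.** **Inputs from the protocol article.** Median baseline albumin 35 g/L, SD 5 g/L, 72 evaluable, 85 recruited (Sample size estimation); margin 5% of the baseline median (Statistical analysis approach); reversion trigger a fall of more than 25% (Discontinuation of study invention).

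**Assumptions.** The article does not say whether the SD of 5 g/L refers to levels or to change; it is read here as the SD of change. The article gives no number of reversions and no recovery after reversion, so both are varied. Bias is treated as a shift in the mean with the SD unchanged.

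**The plan's own figures.**
- Margin: 0.05 × 35 = 1.75 g/L.
- Recruitment: 72 / 0.85 = 84.7, so 85, as stated.
- Sample size for a paired mean, two-sided 5%, 80% power: (5 × (1.960 + 0.842) / 1.75)² = 64.1, so 65, or 67 by the exact t calculation. The stated 72 is slightly larger. The article does not name its formula, and the difference does not affect this point.

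**What the rule needs.**
- Standard error: 5 / √72 = 0.589 g/L.
- Half-width: 1.994 × 0.589 = 1.175 g/L.
- The rule is met only if the observed mean change is above −1.75 + 1.175 = −0.575 g/L.
- With a true mean change of −1.75 g/L and no bias, it is wrongly met 2.5% of the time.

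**Shift from reversion.** A 25% fall from 35 is 0.25 × 35 = 8.75 g/L. If k participants among 72 each recover r g/L by week 28, the mean shifts by k × r / 72. The false-exclusion rate comes from the noncentral t distribution with 71 degrees of freedom and noncentrality shift / 0.589.

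| Recovered participants | Recovery each (g/L) | Shift (g/L) | Share of margin | False-exclusion rate |
|---|---|---|---|---|
| 1 | 2.2 | 0.03 | 2% | 2.8% |
| 1 | 8.75 | 0.12 | 7% | about 4% |
| 3 | 2.2 | 0.09 | 5% | 3.5% |
| 3 | 4.4 | 0.18 | 10% | 4.9% |
| 3 | 8.75 | 0.36 | 21% | about 9% |

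As a proportion, 5% reverted with recovery of 2.2 to 8.75 g/L gives 0.11 to 0.44 g/L. At 10% reverted and full recovery, the shift is 0.10 × 8.75 = 0.88 g/L, half the margin.

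**Loss to follow-up, for comparison.** If 15% have no week-28 value and are left out, the shift is 0.15 × (mean change in those observed minus mean change in those lost). If those lost fell 2 g/L more, it is +0.30 g/L and the false-exclusion rate is 7.3%. If they fell 2 g/L less, it is −0.30 g/L and the rate is 0.7%. The documents do not settle which applies.

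**The case against.** The article fixes continued follow-up, not the analysis set. It does not state that off-device values enter the interval, and the unseen analysis plan may deal with them. Following people after they stop an intervention is normally a strength, because it prevents missing data. The trigger is narrow: two consecutive visits, unexplained falls only. A trigger completed at the week-28 visit comes too late to alter that value. Part of any extreme fall is chance and would recover without a change of dialyser. The planned mixed model, the proportion with a fall above 5% and the individual monitoring of falls above 25% keep large fallers visible.

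Much of this stands, and it limits the likely size. It does not remove the mismatch. The article itself states the rule, its attribution to MCO and the continued follow-up, and nothing in the rule sets off-device values apart. The mixed model and the summaries do not govern the conclusion; the simple interval does.

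A reader might also infer that participants lost to follow-up are omitted and that their loss biases the result toward safety as well. The documents do not support this. "Allowing for a 15% loss to follow-up" is a recruitment allowance, not a completer rule, and handling of missing values may sit in the analysis plan. Loss through death or illness could hide falls. Loss through an unplanned transplant or transfer could be neutral or act the other way.

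**Conclusion.** The point holds for reversion. As written, the rule can credit MCO with albumin values measured on treatments that the article itself says lose less albumin, and the tendency is anti-conservative. The size is conditional. With full 8.75 g/L recovery, 72 evaluable participants and an SD of change of 5 g/L, three recovered participants take the false-exclusion rate from 2.5% to about 9%. With one such participant, or with partial recovery, it stays at about 3% to 5%. A smaller SD of change would make the same shift weigh more.

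The documents do not show that reversions will be common or that recovery will be complete. Bias from loss to follow-up is possible, but neither its sign nor its size is determined.

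**What to change.** 1. State how week-28 albumin measured after reversion counts in the primary conclusion, so that the analysis and discontinuation sections agree.
2. From the mixed model already planned for weeks 4 to 28, estimate the week-28 minus week-4 contrast using only central albumin values taken on MCO, with visit as a category. This also uses up to six values per participant (weeks 6, 8, 12, 16, 20 and 24) that the simple interval leaves out.
3. As a sensitivity analysis, carry the last on-MCO value forward to week 28 for albumin-triggered reversions. This is deliberately pessimistic, because part of an extreme value is chance.
4. Claim that a 5% fall is excluded only if the on-MCO contrast and the interval from all available values agree.

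The change is to analysis wording only. The samples are already scheduled and no clinical rule changes. There are two costs. The on-MCO contrast assumes that values after reversion are missing at random given the central albumin seen before it, which is less secure for discretionary reversions. Requiring agreement also makes the claim slightly harder to reach.
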